## Methods and analysis

### Study design and setting

The present study will be an investigator-initiated, multicentre, double-blind, placebo-controlled, randomised trial including 127 newly diagnosed individuals with type 1 diabetes from 17 study sites in Sweden (online supplemental material). After a run-in period of 2 weeks where blinded CGM is worn to collect baseline variables, study participants will be followed for 12 months after randomisation. Additionally, 1 and 3 years after the end of the treatment period, the participants will be examined during a visit regarding insulin production, glycaemic control, glucose metrics and insulin doses (figure 1). The trial is investigator-initiated and sponsored by the University of Gothenburg, Gothenburg, Sweden. The trial started including study participants in September 2022. The last patient is anticipated to be randomised in May 2025.

**Figure 1 F1:**
[figure not shown]
Study design flowchart.

### Screening

Individuals with type 1 diabetes are monitored at their own clinic and receive verbal or written information about the study during a visit at the hospital, or written information via mail and verbal information via telephone. If individuals are interested in participating, verbal and written informed consent will be obtained from each individual by an investigator (physician) at the study site. During the screening visit, inclusion and exclusion criteria will be examined. Major inclusion criteria are diagnosis of type 1 diabetes and first injection of insulin within 100 days prior to screening, age 18–45 years old, presence of at least one of the autoantibodies (insulin/IAA, GAD-65, ZnT8 or IA-2) at clinical practice or at screening and have a remaining stimulated peak C-peptide >0.20 nmol/L during a mixed meal tolerance test (MMTT). For all inclusion and exclusion criteria, see table 1.

**Table 1 T1:** Inclusion and exclusion criteria

Inclusion criteria	Exclusion criteria
Subjects eligible for inclusion in the study have to fulfil all of the following criteria: Signed informed consent and expected cooperation of the patients for the treatment and follow-up must be obtained and documented according to ICH GCP, and national/local regulations before trial activities are begun. Must be willing and capable of taking the study drugs and meet for tests and follow-up as described. Diagnosed type 1 diabetes (E10.9) within 100 days. First injection of insulin maximum 100 days prior to screening. If aged 36–45 years, a current insulin regimen of both basal and prandial insulin or alternatively use of an insulin pump should exist. Aged 18–45 years old. Presence of antibodies at clinical practice or at screening to at least one of the following antigens: insulin/IAA, GAD-65, IA-2 and ZnT8. Remaining stimulated peak C–peptide ≥0.20 nmol/L. If age 36–45 years, peak C-peptide should be <2.0 nmol/L. Effective contraceptive methods throughout the study.	Subjects fulfilling any of the following criteria are not eligible for inclusion in this study: Contraindications to ixekizumab. Treatment with any oral or injected glucose-lowering agents other than insulin. A history of haemolytic anaemia or significantly abnormal haematology/coagulation results at screening. Participation in other clinical trials with a new chemical entity within the previous 3 months. Subjects with severe obesity (BMI >35 kg/m^2^ if age 18–35 years and BMI >30 kg/m^2^ if age 36–45 years). Subjects with other autoimmune diseases, for example, Mb Crohn, Ulcerative colitis, Graves' disease, psoriasis, psoriatic arthritis and axial spondylarthritis, except coeliac disease and hypothyroidism, which do not need to be excluded. Active serious or chronic infections (ie, in case the patient had a serious infection (eg, pneumonia, cellulitis), has been hospitalised, has received intravenous antibiotics for an infection within 12 weeks prior to screening visit, had a serious bone or joint infection within 24 weeks before screening visit, has ever had an infection of an artificial joint. Known immunodeficiency or patient is immunocompromised to an extent that participation in the study would pose an unacceptable risk to the patient. Active or latent tuberculosis. HIV or active hepatitis B or C. Active or recurrent fungal infection. Subjects with myocardial infarction, stroke, unstable angina or heart failure in the last 6 months. Current clinically significant cardiac arrhythmias as verified by ECG. Planned surgery during the treatment period of the study (except minor surgery on skin lesions, eg, nevus). For female subjects: Positive pregnancy test, presently breast-feeding or unwillingness to use effective contraceptive measures for the duration of the study and 3 months after discontinuation. For male subjects: intent to procreate during the duration of the study or within 3 months after discontinuation or unwillingness of their partner to use effective contraceptive measures for the duration of the study and 4 months after discontinuation. Any history of malignancy in the last 5 years except for completely resected squamous or basal cell carcinoma of the skin. Administration of live attenuated vaccine(s) (LAV) within 2 months of enrolment. Or intended use of LAV during the treatment period. The investigator judges that the clinical diagnosis of type 1 diabetes set is incorrect or uncertain (needs to be confirmed by discussion with experienced diabetologist if excluding due to this criterion) Allergy against ingredients of the investigational products. Known allergy or hypersensitivity to any biologic therapy (active substance or excipients) that would pose an unacceptable risk to the patient if participating in the study. Presence of serious disease or condition, which in the opinion of the investigator makes the patient non-eligible for the study. Liver injury criteria: patients with active hepatobiliary diseases or at screening having alanine aminotransferase (ALT) or aspartate aminotransferase (AST) >2.5 times the upper limit of normal (>2.5 x ULN). Laboratory abnormalities at screening: Neutrophil count <1500 cells/μL (=1,5 *10^9^ cells/ L) Platelet count <100 000 cells/μL (= 100 *10^9^ cells/ L) Haemoglobin <8.5 g/dL (= <85 g/L) (males) and <8 g/dL (= <80 g/L) (women)

* For details regarding contraceptive methods, see online supplemental materials.

### Randomisation

If inclusion criteria are fulfilled, randomisation will take place no later than 8 weeks later. The participants will be randomised to either treatment with an IL-17 inhibitor (ixekizumab) or placebo.

A randomisation list will be created for each participating site. The lists are created by Statistiska Konsultgruppen, Gothenburg, and sent to Tamro AB, Gothenburg, which is responsible for delivering the study medications to each participating site. Only designated personnel from Statistiska Konsultgruppen and Tamro AB will have access to the randomisation lists. If a participant discontinues study participation, their randomisation number will not be reused, and the subject will not be allowed to re-enter the study again.

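### Between screening and first dose no pregnancy test is scheduled, and the numeric laboratory limits and dated infection windows are not applied again at randomisation

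*Protocol article*

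**What the plan says.** The Screening section of the protocol article fixes when eligibility is judged: "During the screening visit, inclusion and exclusion criteria will be examined". Table 2 agrees. The inclusion/exclusion row and the urine pregnancy test row each have a single mark, under Visit 2, and none under Visit 3 (baseline randomisation) or later.

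The Randomisation section then allows an interval: "If inclusion criteria are fulfilled, randomisation will take place no later than 8 weeks later". Under Dose and administration, the 160 mg starting dose is given at week 0.

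Several criteria in Table 1 take screening as their reference point:

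- Infection look-backs: "has received intravenous antibiotics for an infection within 12 weeks prior to screening visit" and "had a serious bone or joint infection within 24 weeks before screening visit".
- Blood counts: "Laboratory abnormalities at screening: Neutrophil count <1500", followed by platelet and haemoglobin limits under the same lead-in, and separately "A history of haemolytic anaemia or significantly abnormal haematology/coagulation results at screening".
- Liver: "or at screening having alanine aminotransferase (ALT) or aspartate aminotransferase (AST) >2.5 times the upper limit of normal".

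Other criteria carry no date. These include a positive pregnancy test, tuberculosis, active or recurrent fungal infection, contraindications to the drug, and the investigator's judgement that a serious condition rules the patient out. Effective contraception is required for the whole study. Table 2 also repeats medical history, concomitant medication, physical examination, haematology, clinical chemistry (which includes CRP) and liver status at Visit 3.

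**The concern.** Entry limits on blood counts, liver enzymes, recent infection and pregnancy protect participants at the moment exposure to an IL-17 inhibitor begins. Here several of them describe the participant at screening, which may be weeks before that moment. Someone who becomes pregnant, or whose ALT or neutrophil count crosses the limit, between Visit 2 and Visit 3 could be randomised and dosed without any departure from the schedule and limits as published. With 17 sites, the same event could also be handled differently from one site to another. The stake is participant safety and consistent conduct, not the estimate of the treatment effect.

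**Working it through.** **Inputs.** The run-in is 2 weeks (Study design and setting), with the masked sensor fitted at the screening visit (Table 2 footnote). Randomisation follows within 8 weeks of the criteria being met (Randomisation). The look-backs are 12 and 24 weeks (Table 1). The first dose is at week 0 (Dose and administration).

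**Step 1: the gap.** The minimum is the 2-week run-in, or 14 days. The stated limit is 8 weeks, or 56 days. That limit runs from fulfilment of the criteria, not from the screening visit. If fulfilment waits for antibody or C-peptide results, the interval from the screening visit to first dose could exceed 8 weeks.

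**Step 2: where the dated windows fall.** A window of W weeks ending at screening, with a gap of g weeks to first dose, covers the period from g to W + g weeks before dosing. It therefore covers W − g of the last W weeks.

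| W | g | Covers, weeks before dose | Share of last W weeks |
|---|---|---|---|
| 12 | 2 | 2 to 14 | 10/12 = 83% |
| 12 | 8 | 8 to 20 | 4/12 = 33% |
| 24 | 2 | 2 to 26 | 22/24 = 92% |
| 24 | 8 | 8 to 32 | 16/24 = 67% |

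The last g weeks before dosing lie outside both windows. These shares show where the windows sit. They do not measure harm.

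**Step 3: rule and test, side by side.**

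| Event in the gap | Rule in Table 1 | Check at Visit 3 in Table 2 | What is left open |
|---|---|---|---|
| New, unrecognised pregnancy | Positive test excludes, undated; contraception required | No pregnancy test | The rule depends on a test that is not scheduled |
| Blood count or liver enzyme worsens | Numeric limits at screening only | Haematology and liver status repeated | The result meets no numeric limit; an ALT of 3 × ULN, for example, would breach none |
| Infection treated with intravenous antibiotics, then resolved | Dated windows end at screening; other limbs may be undated | History, concomitant medication, examination, haematology, CRP | Depends on how the sentence is read |

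The third row needs care. The criterion runs "in case the patient had a serious infection (eg, pneumonia, cellulitis), has been hospitalised, has received intravenous antibiotics for an infection" and then gives the 12-week limit. That limit may govern every limb or only the antibiotic limb. On the second reading, the serious-infection and hospitalisation limbs have no date and could still catch the event.

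Adverse event recording starts with study treatment (Adverse events and safety), so a gap event would appear in the Visit 3 history or bloods and not as an adverse event.

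**The case against.** The strongest reply is that looking back from screening is consistent with judging eligibility at screening, that no section promises a window ending at first dose, and that an article may leave a pre-dose re-check to the full protocol. The first two parts are fair: nothing here contradicts anything else, and this is a design choice that could be better. The third stands only in part. A re-check may exist in a document not shown, but Table 2 is a visit-by-visit schedule that positively places the pregnancy test and the eligibility check in one column, and Table 1 positively chooses screening as the reference point. The point rests on those statements, not on silence.

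Three stronger readings are tempting and should not be drawn:

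- A reader might infer that gap events meet neither a rule nor a test. They do not all go unguarded: laboratory tests, history and examination are repeated at Visit 3, and the pregnancy, active-infection and investigator-judgement exclusions are undated. Each event lacks a dated rule, a numeric limit or a test; none clearly lacks every safeguard.
- A reader might infer that centrally analysed Visit 3 results come back too late to stop the first dose. The article gives no turnaround time, and such detail commonly sits in the full protocol.
- A reader might multiply 127 participants by 8 weeks and call 1,016 participant-weeks the upper bound. The 8 weeks do not start at the screening visit, so that is not a true ceiling, and no distribution of gaps is given.

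**Conclusion.** A minor participant-safety improvement. Followed as published, the plan schedules no pregnancy test between screening and first dose, and it does not apply its numeric laboratory limits or dated infection windows at randomisation. The pregnancy and laboratory parts are firm. The infection part is weaker because it turns on an ambiguous sentence.

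The interval concerned is at least 2 weeks and can reach 8 weeks from fulfilment of the criteria. No number of affected participants can be given, because the article reports no event rates. The conclusion assumes that the run-in starts at the screening visit, that the first dose is given at randomisation, and that no unseen document adds a pre-dose re-check. The primary analysis and sample size are unaffected.

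**What to change.** If recruitment is open:

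- Add an eligibility confirmation and a urine pregnancy test at Visit 3, both before the first dose.
- Apply the existing neutrophil, platelet, haemoglobin and ALT/AST limits to the latest results available before the first dose.
- Count the 12- and 24-week infection windows back from randomisation, and state whether the 12-week limit also covers the serious-infection and hospitalisation limbs.

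The cost is one urine strip per woman, a short checklist and an occasional late screen failure. The blood samples are already scheduled.

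If recruitment is complete, as the anticipated last randomisation in May 2025 suggests, review the Visit 3 history, concomitant medication, examination and laboratory records for gap events, and state in the trial report whether eligibility was re-confirmed before dosing. That costs a record review and one sentence.

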### Lab, monitoring and study drug delivery

The majority of blood samples, including C-peptide levels measured during the MMTT as for the primary endpoint, will be analysed at a central laboratory at the Karolinska University Hospital Laboratory. In brief, centrally analysed blood samples include islet cell autoantibodies, safety blood samples (including renal and liver function), viruses (HIV and hepatitis), thyroid function and coeliac biomarkers.

Only blood samples that require rapid analysis due to transport sensitivity will be handled locally; this includes glycated haemoglobin (HbA1c). The effect on HbA1c is a secondary endpoint and, therefore, must be standardised as much as possible. To ensure consistency, the same laboratory method will be used. In Sweden, all HbA1c methods are calibrated against a central standardisation system via EQUALIS, ensuring comparable HbA1c levels. At the local site, a chest X-ray will also be performed to screen for active/latent tuberculosis.

Biobank samples in whole blood, serum and plasma for all participants will be collected, and in a subsample of participants, also peripheral mononuclear cells.

Each study site will be monitored before the start of the trial, repeatedly during the study and at the end of the trial. Gothia forum, Gothenburg, Sweden, will monitor the trial. No data monitoring committee is used in this study since it is relatively small, short in duration and involves a medication already approved for other indications (eg, psoriasis).

Eli Lilly and Company provides study medication and Tamro AB handles study treatment logistics.

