### Statistical analysis

The full analysis set (FAS-population) consists of all participants who receive at least one dose of study medication and have at least one follow-up measurement.

The per-protocol population (PP-population) consists of all participants in the full analyses set without any significant protocol deviations. The PP-population is defined at the clean file meeting before the database is locked.

The safety population consists of all participants who received at least one dose of study medication.

The primary efficacy variable, difference in change from baseline to week 52 in residual insulin secretion measured by stimulated C-peptide 2 hour area under the curve profile measured by MMTT, will be estimated by ANCOVA adjusting for differences between treatment groups in stimulated C-peptide 2 hour area under the curve at baseline. The secondary efficacy variables (difference in change in insulin need, time in glucose range, time in hypoglycaemia and HbA1c) will also be estimated by ANCOVA adjusting for difference in the evaluated variable at baseline. No interim analyses are planned in the study.

Regarding continuous exploratory variables, the difference between the two groups for normally distributed variables will be analysed using ANCOVA adjusting for baseline value and for not normally distributed variables using Fisher’s non-parametric permutation test. Dichotomous variables will be analysed using Fisher’s exact test and ordered categorical variables using Mantel-Haenszel Chi-square trend test. Statistiska Konsultgruppen, Gothenburg, Sweden, has been consulted for statistical methods.

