### Sample size calculation

In a previous study of 191 individuals with type 1 diabetes followed from diagnosis and year onwards, stimulated c-peptide decreased from 0.70 to 0.46 nmol/L.^6^ The observed SD for c-peptide was 0.34 nmol/L. In two other studies, the SD has been suggested to be 0.25 nmol/L.^22 23^

Using an SD of 0.34 nmol/L, our power calculations indicate that 114 participants would be needed to detect a 25% reduction in c-peptide decline (0.18 nmol/L difference), with two-sided t-test with a power of >80% and significance level of 0.05. If the SD is 0.25 nmol/L, we will also have power to detect a treatment difference of 0.14 nmol/L. We have, therefore, planned to include 114 participants, with an assumed dropout rate of 10%, 127 participants are required.

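### Randomisation lists are made per site, but the stated ANCOVAs leave site out; the likely cost is modest power, and validity is not at risk

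*Protocol article*

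**What the plan says.** Under Randomisation, the article states "A randomisation list will be created for each participating site". Study design and setting gives the scale: "127 newly diagnosed individuals with type 1 diabetes from 17 study sites in Sweden". It does not say whether the lists are blocked, and it gives no allocation ratio.

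Under Statistical analysis, the primary variable "will be estimated by ANCOVA adjusting for differences between treatment groups in stimulated C-peptide 2 hour area under the curve at baseline". The secondary variables (insulin need, time in range, time in hypoglycaemia and HbA1c) "will also be estimated by ANCOVA adjusting for difference in the evaluated variable at baseline". Site appears in neither model, as covariate or random effect. The permutation test for non-normal exploratory variables is also described without site.

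Under Lab, monitoring and study drug delivery, C-peptide is assayed at one central laboratory. HbA1c is measured locally, with a common method and a national calibration scheme.

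**The concern.** If each site's list is blocked, the design holds the arms nearly equal within every site. Differences between sites then largely cancel out of the treatment comparison. A model without site still counts those differences as residual noise, so it reports a standard error larger than the true one. Confidence intervals become too wide and the test rejects too rarely.

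Sites could plausibly differ on the endpoints that depend on local care. Insulin dosing is one, and changes in participants' own CGM use are left to regular clinical care. What is at stake is precision and power. Bias and false-positive results are not at issue.

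**Working it through.** **Inputs from the article.** SD 0.34 nmol/L, difference 0.18 nmol/L, two-sided 5%, 114 evaluable, 127 in total, 17 sites. Average site size is 127/17 = 7.5 randomised, or 114/17 = 6.7 evaluable.

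**Assumptions.** 1:1 allocation. Blocks of 4, or no blocking. The ICC (site share of the variance left after baseline adjustment) runs from 0 to 0.20. The 0.34 is taken as the SD after baseline adjustment.

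**The plan's own figure.** The article says "Using an SD of 0.34 nmol/L, our power calculations indicate that 114 participants would be needed". n per arm = 2 × (1.960 + 0.842)² × 0.34² / 0.18² = 56.01, rounded up to 57, so 114 in total. Exact noncentral-t power at 57 per arm is 0.8001 (at 56 it is 0.793). 114/0.90 = 126.7, rounded up to 127. Both figures reproduce and do not depend on site.

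**Upper bound with perfect balance in every site.** The no-site model reports SE = 2 × 0.34/√114 = 0.0637. The true SE is 0.0637 × √(1 − ICC), so the overstatement is 1/√(1 − ICC) − 1:
- ICC 0.05: 2.6%
- ICC 0.10: 5.4%
- ICC 0.20: 11.8%

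Odd site sizes and unfinished blocks keep a real trial below this bound.

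**Simulation, blocks of 4, even sites, 4,000 trials per row.** The first three results are for the stated model without site.

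| ICC | model SE / true SE | type I error | power, no site | power, fixed site effects |
|---|---|---|---|---|
| 0 | 0.987 | 0.054 | 0.795 | 0.781 |
| 0.02 | 0.990 | 0.054 | 0.803 | 0.797 |
| 0.05 | 1.013 | 0.047 | 0.793 | 0.794 |
| 0.10 | 1.038 | 0.043 | 0.792 | 0.810 |
| 0.20 | 1.093 | 0.033 | 0.817 | 0.863 |

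Simulation error is about √(0.05 × 0.95/4000) = 0.003 for type I error, √(0.8 × 0.2/4000) = 0.006 for power, and 1/√8000 = 1.1 percentage points for the SE ratio. Uneven sites gave SE ratios of 1.020, 1.031 and 1.090 at ICC 0.05, 0.10 and 0.20.

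**Unblocked lists.** Over all ICC values and both site patterns, the no-site model had SE ratios of 0.98 to 1.00 and type I errors of 0.047 to 0.056. The test is not conservative here. At ICC 0, fixed site effects cut power from 0.787 to 0.720 (even sites) and from 0.803 to 0.742 (uneven), a loss of 6 to 7 points.

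**Random site intercept, 5,000 trials per row, even sites.**

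| lists | ICC | power, no site | power, random intercept | change in points |
|---|---|---|---|---|
| blocks of 4 | 0 | 0.807 | 0.811 | +0.4 |
| blocks of 4 | 0.05 | 0.797 | 0.811 | +1.4 |
| blocks of 4 | 0.10 | 0.815 | 0.838 | +2.3 |
| blocks of 4 | 0.20 | 0.822 | 0.877 | +5.5 |
| unblocked | 0 | 0.796 | 0.794 | −0.2 |
| unblocked | 0.20 | 0.799 | 0.844 | +4.5 |

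A further 2,000 trials per scenario gave gains of about 1, 2.5 and 5.6 points at ICC 0.05, 0.10 and 0.20 with blocks. The random intercept lost no power beyond simulation error in any scenario. At ICC 0 with blocks its type I error was 0.053, against 0.051 without site.

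**The case against.** A reader might infer from one list per site that the standard errors are too large and the tests too conservative as a matter of fact. The documents do not support that. A separate list does not by itself balance the arms within about seven participants. Blocking does that, and the article does not mention blocking. Conservatism also needs sites that still differ after baseline adjustment, which takes up much of any stable site difference, and no between-site variance is given.

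Nor does local measurement of HbA1c show a material site effect, since the same section describes a common method and central calibration. C-peptide is assayed centrally, and the CGM endpoints come from one masked device type. At an ICC of 0.05 or less, the effect on the standard error is hardly distinguishable from simulation error. All of this stands, and it makes the size conditional.

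It can also be said that handling of site belongs in the full protocol or SAP, which are not shown. That holds for block size. It holds less well for the model: the article states the adjustment for the primary and secondary analyses, and site is not part of it. A fuller document may add site, in which case the point is met.

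The warning that site terms can cost power is right for 16 extra fixed parameters. It does not apply to a random intercept.

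**Conclusion.** The mismatch between site-wise randomisation lists and models without site is plain in the text. Its consequence is conditional.

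If the lists are blocked, the model SE is about 0–2% too large at an assumed ICC of 0.05, about 1–5% at 0.10 and about 8–11% at 0.20, where the type I error is about 0.033. The power forgone is about 1, 2–3 and 5–6 points. If the lists are unblocked, the stated test keeps its nominal level and only some precision is lost.

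In no case is validity threatened. The loss deserves attention because the sample-size calculation, "with two-sided t-test with a power of >80% and significance level of 0.05", gives 0.8001 at 114 evaluable participants. That calculation takes no credit for baseline adjustment, so actual power may be higher. Severity: minor.

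**What to change.** Before unblinding, state that site enters the primary and secondary models as a random intercept beside the baseline value, or justify leaving it out. State also whether the lists are blocked. If the estimated site variance is zero, the model reduces to the ANCOVA already planned.

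Do not use 17 unpooled fixed site effects: with unblocked lists and no site differences they can cost 6 to 7 points of power. If fixed effects are preferred, pool the smallest sites by a rule set before unblinding.

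In any permutation test, permute treatment labels within site.

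The cost is a sentence or two in the analysis plan, a little extra analysis work and, at most, a very slight rise in type I error when the site variance is near zero. Sample size does not change.
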